### Therapists

All therapists (n = 16) participating in this study work at one of the three agencies. Two therapists are mental health workers and 14 therapists are graduated psychologists of which 12 have a registration as a Health Care psychologist ('GZ-psycholoog'). Seven therapists are between 25 and 40 years old. Five therapists are between 40 and 55 years old, and four therapists are older. Years of experience of the therapists varies between three and 27 years. At each institution the therapists will be randomly assigned to the experimental or control condition. The therapists in the experimental condition will participate in a two-day training in the protocol provided by the author of the manualized protocol, [name]. In this training the protocol will be explained and practiced on each other during exercises and role-plays. The therapist in the control condition will receive no extra training.

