### Participants

Child-participants between the age of eight to twelve years will be recruited at one of the agencies. As part of the usual intake procedure families are asked to fill in standard questionnaires to collect information for diagnostic assessment and indication criteria. When a child is between eight and twelve years old additional questionnaires will be administered. These are: the Child Behavior Checklist (CBCL), the Teacher Report Form (TRF) and the Screen for Child Anxiety Related Emotional Disorders (SCARED) and are meant to assess children's level of anxiety and to determine the presence of additional problems. Inclusion criteria are a score above the clinical cut-off on either the child or parent version of the SCARED-NL total scale or one of the following subscales: generalized anxiety, social anxiety, separation anxiety and panic disorder. Exclusion criteria are autism, post traumatic stress syndrome, specific anxiety disorder, obsessive-compulsive disorder and an IQ below 80. Medication is allowed and will be assessed during the measurement waves.

Families with an eligible child will be informed about the project by one of the researchers and will be asked to participate. When a family agrees to participate, they fill in an informed consent form. Families will be randomly allocated to the TDD or TAU condition using a blocked randomization scheme (block size 4). Randomization will be done by an independent researcher at the Behavioural Science Institute.

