### Sample size calculation

The study aims to assign 120 anxious children to the project. The children will be equally divided across both conditions. Power analysis (G-power) is based on a 3-month effect size of 1.0 taking into account a maximum of 20% attrition over time and loss of power due to multiple imputation. Sample sizes will be 60 families per condition (alpha < .05, power = .80). For testing the effect of the potential mediators, we do not need to run a RCT per se. However, as we are the first running a follow-up study on Bodden et al. [13], it is essential to establish whether we will obtain similar effect sizes. Hence, we can not estimate the variability in the mediators beforehand - as this has not been examined in these kinds of CBT treatments before - but previous work on other types of pathology [44] and the high effect size necessary to examine differences at all, provide us with confidence that our design and sample size is suitable. The sample sizes are large for observational treatment studies involving parent-child interactions [45]. Excellent observational studies with similar or smaller sample sizes have been published in top-tier journals. This is largely due to the fact that micro-coding in observational designs holds repeated measurements of individual variables [46].

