### Statistical analyses

In accordance with the intent-to-treat philosophy, all children randomized to a condition will be included in the analyses to test the study hypotheses. Analyses will be conducted using Mplus, which is a statistical modeling program that has special features to deal with missing data and it allows analyses with complex data while taking into consideration the longitudinal character of the data. Regression analyses will be conducted to test whether children in the experimental condition (TDD) show a stronger decrease in anxiety symptoms than in the control condition (TAU). Also for the second aim of our study, namely testing whether secondary problem behavior (i.e. aggression, depression) decreases more in the experimental condition, regression analyses will be conducted. Third, to investigate the mediating role of alliance and parenting, mediation analyses will be performed in Mplus, using bootstrap methods.

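### Therapists are randomised to arms and so nested in them, but neither the stated regressions nor the sample size allows for therapist clustering, which puts the type I error and confidence intervals at risk

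*Protocol article*

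**What the plan says.** The protocol article allocates two kinds of unit.

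- **Families** (Participants): "Families will be randomly allocated to the TDD or TAU condition using a blocked randomization scheme (block size 4").
- **Therapists** (Therapists): "All therapists (n = 16) participating in this study work at one of the three agencies", and "At each institution the therapists will be randomly assigned to the experimental or control condition". Those in the TDD arm get a two-day training; for the others, "The therapist in the control condition will receive no extra training".

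The analysis and the sample size are then described without reference to therapists.

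- **Statistical analyses:** "Regression analyses will be conducted to test whether children in the experimental condition (TDD) show a stronger decrease in anxiety symptoms" than under TAU. The same method is named for secondary outcomes, and bootstrap mediation analyses for alliance and parenting. The data features mentioned are missing values and repeated measurement over time. The section also remarks that Mplus can analyse complex data.
- **Sample size calculation:** "Power analysis (G-power) is based on a 3-month effect size of 1.0 taking into account a maximum of 20% attrition over time", together with an unquantified loss from multiple imputation. The result is "Sample sizes will be 60 families per condition (alpha < .05, power = .80").

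**The concern.** A therapist assigned to one condition, with training given in one condition only, treats children in that condition only. This is an inference from the Therapists section, but a direct one. Therapist is therefore nested in arm, and differences between therapists add to the variance of the difference between arms. A regression that treats the children as independent leaves that component out of the standard error.

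The document gives reasons to expect some variation between therapists. Experience runs from 3 to 27 years, two of the 16 are mental health workers rather than psychologists, and under TAU each therapist chooses the treatment without restriction.

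At stake is the main comparison of TDD with TAU. Its p-value would be too small and its confidence interval too narrow, in a trial whose Discussion looks ahead to large-scale roll-out. The alliance analyses are exposed in the same way, since the WAI-S is completed by the therapist and one therapist rates several children.

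**Working it through.** **Inputs from the protocol article:** 16 therapists; 60 children per arm; up to 20% attrition, so 60 × 0.8 = 48 completers per arm; planned effect d = 1.0; alpha 0.05; power 0.80.

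**Assumptions, not in the document:** a two-sided test; 8 therapists per arm; equal caseloads, so m = 60/8 = 7.5 children per therapist, or 48/8 = 6 after attrition; therapist ICC from 0.01 to 0.20.

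**The plan's own figure.** A two-sided t test for d = 1.0 at 80% power needs 17 per arm, and 17/0.8 = 21.25, so 22 after attrition. The stated 60 is not reproduced. That is a separate matter, but it explains the large surplus of power below.

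**Formulas**

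- Design effect: DE = 1 + (m − 1) × ICC
- True SE / naive SE = √DE
- Real error of a nominal 5% test = 2 × [1 − Φ(1.96/√DE)]
- Power at d = 1.0: noncentral t on 16 − 2 = 14 df, noncentrality √(n_eff/2), where n_eff = n/DE

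**60 per arm, m = 7.5**

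| ICC | DE | √DE | Real type I error | n_eff per arm |
|---|---|---|---|---|
| 0.01 | 1 + 6.5 × 0.01 = 1.065 | 1.03 | 5.8% | 56 |
| 0.05 | 1.325 | 1.15 | 8.9% | 45 |
| 0.10 | 1.65 | 1.28 | 12.7% | 36 |
| 0.20 | 2.30 | 1.52 | 19.6% | 26 |

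**48 per arm, m = 6**

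| ICC | DE | Real type I error | n_eff per arm | Power at d = 1.0, therapist-level test |
|---|---|---|---|---|
| 0.01 | 1 + 5 × 0.01 = 1.05 | 5.6% | 46 | 99% |
| 0.05 | 1.25 | 8.0% | 38 | 98% |
| 0.10 | 1.50 | 11.0% | 32 | 96% |
| 0.20 | 2.00 | 16.6% | 24 | 90% |

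**Simulation check** (40,000 null trials per case). The naive t test at 60 per arm rejected in 8.6%, 12.8% and 19.9% of trials at ICC 0.05, 0.10 and 0.20. A t test on therapist means with 14 df rejected in 4.9% in each of these cases.

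**Unequal caseloads.** With a coefficient of variation of 0.5, DE = 1 + (1.25 × 7.5 − 1) × ICC. At ICC 0.05 this is 1.419, and the real error is about 10%. At 48 per arm and ICC 0.20, power at d = 1.0 falls to 85%, still above the planned 80%.

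**Cluster-robust variance without correction.** With 16 clusters, equal caseloads and a normal reference distribution, the simulated error is 8.5% to 9.0%. Robust errors alone therefore do not solve the problem.

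**The case against.** **The plan is silent, not wrong.** This is the strongest objection. The article nowhere says that children are treated as independent, names no level for the regression, and a statistical analysis plan that is not shown could add a therapist term. This stands as far as it goes: the result is conditional on the regressions being run as described. It does not dispose of the point. The article itself creates the nesting, then names the model type, the data features to be respected and the allowances in the sample size, and none of these is about therapists.

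**The remark on complex data covers it.** The remark describes what the software permits and commits to no adjustment. It is ambiguous, however. It should not be read as referring to repeated measures only.

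**The ICC is unknown.** This stands. At ICC 0.01 the real error is 5.8%, close to nominal. The direction is certain for any positive ICC; the size is not.

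Three stronger readings are tempting, and the document does not support them.

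- *The trial loses its power.* A reader might infer this from the missing design effect. At the planned d = 1.0, power stays at about 90% or more with 48 per arm and equal caseloads up to ICC 0.20.
- *Therapist differences bias the comparison.* Therapists are randomised within each institution, so their differences add variance, not systematic bias.
- *The mediation bootstrap resamples individual children.* The resampling unit is not stated. Alliance is also rated by the child on the TASC, so the shared-rater problem concerns the WAI-S.

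**Conclusion.** The concern holds in conditional form. Therapist is nested in arm by design, and the analysis and sample size as stated make no allowance for it. If the regressions are run that way, the standard error for TDD versus TAU is understated by a factor of 1.03 to 1.52 over ICC 0.01 to 0.20 at 60 per arm. A nominal 5% test then has a real error of about 6%, 9%, 13% and 20% at ICC 0.01, 0.05, 0.10 and 0.20. These figures rest on 8 therapists per arm, equal caseloads of 7.5 and an assumed ICC; unequal caseloads make them worse. The harm is to the type I error and the confidence intervals, and surplus power does not cure it.

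**What to change.** 1. **Primary and secondary outcomes:** fit a two-level model with a random therapist effect nested in arm, agency as a fixed effect (therapists are randomised within agency), and a small-sample correction for 16 clusters. The degrees of freedom are about 14, slightly fewer once agency is fitted. Satterthwaite or Kenward-Roger would serve; a cluster-robust variance with a small-sample correction is an acceptable alternative. If Mplus does not offer the correction, run this analysis in other software.
2. **Mediation:** carry the therapist level into the model or resample therapists, and state the bootstrap unit.
3. **Sample size calculation:** state a therapist ICC range and the resulting design effect, with the assumed number of therapists per arm and caseload.

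The cost is a therapist identifier in the dataset, revised wording, and somewhat wider confidence intervals. No further children or assessments are needed, because power at d = 1.0 remains above 80%.

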### Intervention

#### Experimental condition

The experimental condition (TDD) consists of twelve weekly sessions with the child and three sessions with the parents. In the first session the rationale behind cognitive behavior therapy will be explained to the child and its parents. During the second session the child learns to identify his anxious thoughts and how to generate alternative thoughts. Challenging anxious thoughts is also discussed. Relaxation and mind-distraction is practiced in the third session. In the same week as the third session, a parent session is taking place where the parent will be made aware of the influence of their own fear on the behavior of the child. Parents are also taught how to support their child in every step it takes facing his fear. In the fourth session children make a hierarchy of anxious situations they want to face during therapy. Also, self rewarding is explained in this session. Exposure to the anxious situations starts in session five and lasts until session ten. In the same week as session six, the second parent session is scheduled. Parents will be taught how to support their child during exposure tasks. Their thoughts about their child will be discussed and challenged. In the seventh and eighth session challenging thoughts will be illustrated by doing an experiment in which the child learns to restructure his thoughts. In session nine the child will be motivated to talk more with his parents about its fear. The parents are also motivated to communicate more with their child about anxiety and with each other about their parenting styles. It will be explained how spouses can support each other. A summary of the learned skills during therapy is given in session ten. The last exposure task is a game or a quest. How the child should deal with set backs is discussed in session eleven. In the last session, session twelve, the therapy ends by giving the child a certificate. How the child can deal with new anxious situations without the therapist is also discussed. Each month after this session the therapists will make a phone call to stimulate the child to keep using the learned skills. Three months after session twelve a follow-up session is held with the child and his/her parents. The therapy, the change in behavior of the child and the learned skills will be evaluated. Each therapy will be supported by a therapist manual, and child and parent workbooks. Within three months this treatment will be completed.

#### Control condition

Children and families in the control condition (TAU) will receive treatment that is being normally given at each institution during the period of three months. There are no restrictions for this condition and we will track the types of interventions provided. The therapist will decide what the treatment should be. Usually therapy for anxious children consist of various sessions in which therapists use different parts of protocols or from their own clinical experience, mostly based on cognitive restructuring, exposure tasks and relaxation tasks with the child and a few sessions with the parents. Sometimes other techniques such as EMDR (Eye Movement Desensitization and Reprocessing) or Mindfulness are used.

### Data collection

In order to compare our findings with those of Bodden et al [13] we will use similar instruments for both child and mother. The anticipated flow of data collection is graphically shown in Table 1. All therapy sessions will be audio-taped. For treatment integrity, three sessions per client will be randomly selected and coded. We will use coding measures of [name] to track treatment integrity.

#### Outcomes

The primary outcome, anxiety symptom level, will be measured with the SCARED-NL [28], a screening instrument for children. The child self-report (C) and parent-report (P) version consist of 69 identical items which differ only in the substitution of you/your child. Mother and child score each item on a 3-point scale ranging from 0 (never or almost never) to 2 (often). The SCARED-NL demonstrates good convergent and divergent validity compared with psychiatric diagnoses and/or structured psychiatric interviews [29,30].

Secondary outcome measures are depression and aggression which will be assessed with the Child Behaviour Checklist (CBCL; [31]) and the Teacher Rate Form (TRF; [32]). Both questionnaires describe a wide domain of internalizing and externalizing behavior problems of children. The CBCL consists of 113 items and the TRF consists of 118 items; ninety-three items are overlapping. Both mother and teacher are asked to rate each item on a 3-point scale ranging from 0 (does not apply to the child) to 2 (clearly or often). The checklist provides T-scores for internalizing and externalizing behavior. Both the CBCL and the TRF show satisfactory psychometric properties [33].

Therapeutic alliance between therapist and child will be measured with two alliance questionnaires. The therapist will fill in the Dutch translated version of the Working-Alliance-Inventory-Short Form (WAI-S; [34,35]). The WAI-S was developed to measure Bordin's three aspects of alliance: the bond, agreement of tasks-, and goals [36,37]. The scale consists of 12 items on a 7-point scale. Research has demonstrated the reliability and validity of the scale [38,39].

The child will be asked to fill in the Dutch translated version of the Therapeutic Alliance Scale for Children (TASC-nl; [40]). The TASC-nl includes 12 items which have to be completed on a 4-point scale ranging from 1 (not at all) to 4 (very much). The TASC was designed specifically for the use with children and adolescents. Positive and negative aspects of the therapeutic alliance are measured. In previous research the TASC has demonstrated adequate internal consistency (a = .72 to.74) [40,41].

The possible mediator parenting will be assessed through observations of structured mother-child interactions [42,43], taking place in the homes of the families at a time convenient for them. Interactions will be videotaped and subsequently coded for the dimensions rejection and control. In the study the focus is on mothers, since they are in most cases the primary caregiver and we want to standardize across participants and measurement waves. A standardized paradigm will be used for observations of mother-child interactions. Mother and child will engage in three 5-minute episodes: (1) a competitive sports game on the Nintendo Wii console, (2) a discussion about something the child is anxious about in the coming week, and (3) a cooperative sports game on the Nintendo Wii console The digital video recordings will be coded using Noldus Observer XT. Three assistants will be trained to reliably code videos for the dimensions rejection and control. Assistants will be intensively trained to a minimum criterion of 75% agreement and 0.65 kappa using a frequency/sequence-based comparison and a criterion of 80% agreement using a duration/sequence based comparison. Recalibration training will be conducted to minimize coder drift. A second coder for reliability purposes will code 20% of all sessions. Coders will be blind to which sessions will be used to assess observer agreement and also blind to the condition and when in the treatment protocol the observations were collected (pre, post or follow-up).

### Sample size calculation

The study aims to assign 120 anxious children to the project. The children will be equally divided across both conditions. Power analysis (G-power) is based on a 3-month effect size of 1.0 taking into account a maximum of 20% attrition over time and loss of power due to multiple imputation. Sample sizes will be 60 families per condition (alpha < .05, power = .80). For testing the effect of the potential mediators, we do not need to run a RCT per se. However, as we are the first running a follow-up study on Bodden et al. [13], it is essential to establish whether we will obtain similar effect sizes. Hence, we can not estimate the variability in the mediators beforehand - as this has not been examined in these kinds of CBT treatments before - but previous work on other types of pathology [44] and the high effect size necessary to examine differences at all, provide us with confidence that our design and sample size is suitable. The sample sizes are large for observational treatment studies involving parent-child interactions [45]. Excellent observational studies with similar or smaller sample sizes have been published in top-tier journals. This is largely due to the fact that micro-coding in observational designs holds repeated measurements of individual variables [46].

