## Methods/Design

### Trial design

The effectiveness of the TDD program will be tested in a RCT in which three Dutch community mental health agencies (Pro Persona Youth in Nijmegen and Arnhem and the Ambulatorium Nijmegen) will participate. A total of 120 clinically anxious children (8 - 12 years old) and their parents will participate in this study after filling in a consent form (see Figure 1 for the study design). The participants will be randomly allocated to the experimental (TDD, *N *= 60) or control condition (TAU, *N *= 60). The TDD consists of twelve weekly sessions with the child and three sessions with the parents. The treatment is supported with child, parent and therapist manuals. Children in the control group will receive the treatment that is usually delivered in those agencies. This means that these children will receive the treatment that the therapist considers to be the most effective treatment for that particular child. Baseline assessments, post-treatment, a six-month follow-up and a one year follow-up will be conducted among children, mothers and therapists and through direct observations (see Table 1).

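### The stated power of .80 does not belong to an effect size of 1.0 with 60 families per arm; the discrepancy is conservative, and the detectable effect should be restated

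*Protocol article*

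**What the plan says.** The Sample size calculation section of the protocol article gives one effect size and an attrition allowance: "Power analysis (G-power) is based on a 3-month effect size of 1.0 taking into account a maximum of 20% attrition over time". The same sentence names a second allowance, for power lost through imputing missing data, and attaches no value to it. The result is then given as: "Sample sizes will be 60 families per condition (alpha < .05, power = .80". The arms are to be equal in size, and the Abstract and the Trial design section repeat 60 per arm.

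The section does not name the test or its sidedness. It does not say whether 1.0 is a difference between the two arms or a change within one arm. It makes no allowance for clustering by therapist, although the Therapists section describes 16 therapists and says "At each institution the therapists will be randomly assigned to the experimental or control condition".

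**The concern.** An effect of a full standard deviation is large, and a two-arm comparison with 80% power for it needs few children. Sixty per arm is almost three times what the quantified inputs require. So at least one of these holds: the effect size is not the one that was used, the power is not .80, or the unquantified allowance is carrying most of the sample size.

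What is at stake is interpretation. The comparator is active: the Control condition section describes usual care as mostly cognitive restructuring, exposure and relaxation. The Background's effect sizes of 1.39 and 1.03 come from a trial that included a waitlist arm. Effects well below 1.0 against usual care are therefore of real interest, and the reader needs to know which of them this trial can detect. As printed, a null result looks informative only about effects near 1.0.

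**Working it through.** **Inputs.** From Sample size calculation: effect size 1.0, alpha .05, power .80, attrition at most 20%, equal arms, 60 per arm. From Therapists: 16 therapists, so 8 per arm if evenly split. *Assumed, because the article does not say:* 1.0 is a between-arm difference d; the test is a two-sample t-test, two-sided (one-sided also tried).

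**Step 1: try to reproduce 60 per arm.** With n per arm, the t statistic has 2n − 2 degrees of freedom and noncentrality d√(n/2).

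- Two-sided, d = 1.0: n = 16 gives power .781 and n = 17 gives .807, so 17 evaluable per arm. After attrition, 17 / (1 − 0.20) = 21.25, so **22 per arm**.
- One-sided: 14 evaluable; 14 / 0.80 = 17.5, so **18 per arm**.

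Neither reproduces 60.

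**Step 2: how large would the imputation loss have to be?** Sixty enrolled with 20% attrition leaves 60 × 0.80 = 48 evaluable. Since 17 suffice, imputation would have to remove 1 − 17/48 = 0.646, about **65%** of the information left after attrition. Required enrolment per arm for assumed losses L is 17 / 0.80 / (1 − L):

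| Assumed loss L | Per arm |
|---|---|
| 10% | 24 |
| 20% | 27 |
| 30% | 31 |
| 50% | 43 |

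**Step 3: other routes to 60.**

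- Attrition of 20% compounded over three waves: 17 / 0.80³ = 33.2, so 34. Over four waves: 17 / 0.80⁴ = 41.5, so 42. Both are more generous than the text, which gives 20% as the maximum over time.
- A therapist design effect 1 + (m − 1) × ICC would have to equal 48/17 = 2.82. That needs ICC = 1.82/6.5 = 0.28 with m = 7.5 children per therapist (60/8), or 1.82/5 = 0.36 with m = 6 evaluable (48/8). The section states no such allowance.
- A within-group effect of 1.0 in a paired test needs about 10 children, so that reading does not give 60 either.

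**Step 4: what 60 per arm delivers.**

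| Evaluable per arm | Power at d = 1.0 | d at 80% power, two-sided | d at 80% power, one-sided |
|---|---|---|---|
| 48 | 99.8% | 0.58 | 0.51 |
| 60 | 99.97% | 0.52 | 0.46 |

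For 48 per arm the required noncentrality is 2.83, and 2.83 × √(2/48) = 0.578.

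**Step 5: sensitivity to therapist clustering.** The article gives no ICC; .05 and .10 are assumptions. With 6 evaluable children per therapist the design effect is 1 + 5 × .05 = 1.25 or 1 + 5 × .10 = 1.50.

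- Usual design effect: 0.578 × √1.25 = 0.65 and 0.578 × √1.50 = 0.71.
- If the test also uses 14 therapist-level degrees of freedom (16 − 2), the required noncentrality is 3.01: 3.01 × √(2 × 1.25/48) = 0.69 and 3.01 × √(2 × 1.50/48) = 0.75.

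**The case against.** Five points can be made for the plan.

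*There is a further stated allowance.* The imputation loss is named, so strictly the calculation cannot be reproduced because one input has no value. That stands. It does not rescue the figure, because no plausible loss closes the gap. Nor should one claim that imputation can never cost power: a finite number of imputations adds some variance, though far less than 65%. Asking for the value is therefore fairer than insisting that the allowance be deleted.

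*The meaning of 1.0 is open.* The section wants to see whether effect sizes similar to those of the earlier trial are obtained, and does not define them as differences from usual care. If 1.0 is a within-group change, the fault lies in the choice of effect size rather than in the arithmetic. That stands too, and it is why the definition must be stated.

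*The sample also serves the mediation analyses.* This makes a larger N unsurprising, but it does not attach power .80 to an effect of 1.0.

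*Nothing in the conduct of the trial changes.* Randomisation, outcomes, analysis and enrolment are untouched, and a reported confidence interval would limit the misreading of a null result. This lowers the severity.

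*The discrepancy is conservative.* A reader might infer from a wrong power figure that the trial is underpowered, or from 22 per arm that enrolment should be cut. The documents support neither. At the stated effect the planned N gives more than the stated power, and a smaller trial would lose the ability to detect the more modest differences that matter against an active comparator.

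**Conclusion.** The point holds in limited form. Under a standard two-sample comparison, a between-arm effect of 1.0, power of .80 and 60 per arm with at most 20% attrition do not fit together, and the unquantified imputation allowance cannot plausibly make them fit. The quantified inputs give 22 per arm two-sided or 18 one-sided. Conversely, the planned N has about 99.8% power at d = 1.0 and reaches 80% at about d = 0.58.

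This rests on reading 1.0 as a between-arm d, on a t-test at two-sided .05, and on independent observations. Allowing for therapists moves the detectable effect up, by an amount that depends on an ICC the article does not give. The defect is in the stated justification and not in the size of the trial: should-fix.

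**What to change.** Keep N = 120 and replace the power sentence by what the design delivers, for example: *With 60 families per arm and up to 20% attrition (48 per arm), the trial has 80% power at two-sided alpha .05 to detect a between-arm difference of d = 0.58, before any allowance for therapist clustering.*

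In the same place, name the test and its sidedness, say whether 1.0 was a between-arm or a within-group effect and where it came from, and either give the imputation allowance a value or drop it. If a clustered figure is added, label it with its assumed ICC and its method: 0.65 to 0.71 with the usual design effect, or 0.69 to 0.75 with 14 therapist-level degrees of freedom, both for ICC .05 to .10 and 6 evaluable children per therapist.

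The cost is one or two rewritten sentences, with no change to enrolment, data collection or analysis.

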In a study by Bodden, [name] and colleagues [13] the effectiveness of the TDD-treatment was tested with a randomized controlled trial including three different conditions. Children were between eight and 17 years old and either received the TTD (individual CBT with little parental involvement), a family CBT or were put on the waitlist for eight weeks. Some of the families in the waitlist condition received the treatment after eight weeks. These post waitlist results were included in the effect calculation. At post-treatment 41% of the children was free of all anxiety disorders and 56% was free of their primary anxiety diagnosis. All waitlist children still had anxiety disorders after the waitlist period. At three-month follow up these percentages were 52% and 67% respectively. Concerning the difference between the TTD and the family CBT, the study found better treatment outcomes for the TDD (56% recovered from anxiety) compared to the family CBT (28% recovered from anxiety). The effect size for the TDD was 1.39 and 1.03 for the family CBT (as measured with the parent version of the dutch version of the Screen for Child Anxiety Related Emotional Disorders (SCARED-NL). In families where parents had an anxiety disorder, children also benefited more from the TDD (46% recovered from anxiety at post treatment) compared to family CBT (19% recovered from anxiety at post treatment). Also, more dropouts were found in the family CBT-condition (19%) than in the TDD (3%). In sum, the effect sizes of the TDD program are promising and based on this study's results the TDD, that is an individual CBT with little parental involvement, seems to be more beneficial than a family CBT. The child and therapist manuals of the TDD are published including assessments and treatment integrity forms, and the program is now widely used in the Netherlands.

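### The planning effect of 1.0 is not justified for TDD versus an active, largely CBT-based TAU, and the stated 80% power fits neither that effect nor the contrast tested

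*Protocol article*

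**What the plan says.** Protocol article, Sample size calculation: "Power analysis (G-power) is based on a 3-month effect size of 1.0". The allowances made in this calculation are described as "taking into account a maximum of 20% attrition over time and loss of power due to multiple imputation". The result is given as "Sample sizes will be 60 families per condition (alpha < .05, power = .80"). Neither the source nor the comparator of the 1.0 is stated. Later in the section the authors say that "it is essential to establish whether we will obtain similar effect sizes", with reference to the earlier TDD trial.

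Background describes that trial as having three arms: TDD, family CBT and an eight-week waitlist. It reports: "The effect size for the TDD was 1.39 and 1.03 for the family CBT", on the parent version of the SCARED-NL. Of the waitlist it says: "All waitlist children still had anxiety disorders after the waitlist period". Background also gives 0.86 as the mean CBT effect in a meta-analysis of 24 studies.

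The present trial tests TDD against TAU (Aim and hypotheses; Statistical analyses). Under Control condition, TAU is the therapist's choice over the same three months, "mostly based on cognitive restructuring, exposure tasks and relaxation tasks with the child and a few sessions with the parents", sometimes with EMDR or mindfulness. Strengths and limitations presents TAU, rather than a waitlist, as the stronger test of the program.

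**The concern.** A sample size calculation should use the expected difference between the two arms being compared. The 1.0 lies among effects quoted for CBT overall and from a waitlist-controlled trial, but the comparator here is active treatment that shares much of TDD's content. The article itself regards this as a harder test, yet gives no sign that the planning effect was lowered for it.

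The stated 80% also ought to follow from the stated effect, alpha and N. If it does not, a reader cannot tell what difference the trial is able to detect. This matters because the article links wider implementation to TDD proving better than usual care. A statement of 80% power at 1.0 gives no indication of how the trial performs at the smaller differences that are plausible between two active treatments.

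**Working it through.** **Inputs.** From Sample size calculation: d = 1.0, alpha .05, power .80, attrition up to 20%, 60 per arm, equal allocation. Sidedness is not stated; two-sided is assumed and one-sided is also tried. The loss from multiple imputation is mentioned but not quantified.

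**Step 1: try to reproduce 60 per arm.**
- Normal approximation: n = 2(z₀.₉₇₅ + z₀.₈₀)²/d² = 2(1.960 + 0.842)²/1.0² = 15.7, so 16 per arm. The exact noncentral-t calculation gives 17.
- After 20% attrition: 16/0.8 = 20; 17/0.8 = 21.25, so 22.
- One-sided: 13 (normal) or 14 (t), which become 17 or 18 after attrition.

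No variant gives 60. For the imputation allowance to close the gap it would have to multiply N by 60/22 = 2.7 to 60/20 = 3.0, on top of the attrition allowance.

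**Step 2: power of the planned size at d = 1.0 (noncentral t, two-sided).**
- 60 per arm: above 99.9%.
- 60 × 0.8 = 48 per arm: 99.8%. As a check, the normal approximation gives 1.0 × √(48/2) − 1.960 = 2.94, and Φ(2.94) = 99.8%.

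**Step 3: the difference for which 80% power is true.**
- Normal approximation: d = 2.802 × √(2/n), which is 0.57 at 48 per arm and 0.51 at 60.
- Noncentral t: 0.58 at 48 per arm and 0.52 at 60.

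**Step 4: power over a range.** The article gives no TDD-versus-TAU difference, so the values of d below are assumptions. Power is by noncentral t, two-sided; the last column uses the normal approximation.

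| Assumed d | Power, 48 per arm | N per arm for 80% power, incl. 20% attrition |
|---|---|---|
| 0.6 | 83% | 55 |
| 0.5 | 68% | 79 |
| 0.4 | 49% | 124 |
| 0.3 | 31% | 219 |

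Steps 2 to 4 do not include imputation loss, clustering by therapist or any gain from baseline adjustment.

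**The case against.** **The design has slack.** This stands. Because 60 per arm far exceeds what d = 1.0 requires, the unsupported effect does not by itself put power below 80%. That happens only if the true TDD-versus-TAU difference is under about 0.58, and the article does not say what that difference is.

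**The simple t-test may be pessimistic.** If the planned regression adjusts for baseline and the correlation with outcome is .5 (an assumption), the effective d at 0.50 is 0.50/√(1 − .5²) = 0.58, and power at 48 per arm rises from 68% to about 80%. This also stands, though imputation loss and therapist clustering would work in the other direction.

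**The remark about similar effect sizes may not be a power assumption.** It sits among sentences on the mediators and can be read as an aim to replicate TDD's own effect. That is fair. The point therefore rests on the 1.0 in the power statement.

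**A stronger reading that the article does not support.** A reader might subtract the two earlier effects, 1.39 − 1.03 = 0.36, take this as the expected TDD-versus-TAU difference, and conclude from the 41% power at 48 per arm that the trial will probably miss its effect. But 0.36 contrasts TDD with family CBT, not with an unrestricted TAU chosen by the therapist. Background does not say whether the two effects are within-arm or against waitlist, and subtracting them requires a common standardiser. They also come from parent reports at ages 8 to 17, whereas this trial uses child and parent reports at ages 8 to 12. So 0.36 is one possible value within an assumed range.

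**Conclusion.** The point holds in two parts. First, an effect of 1.0 has no stated basis for TDD against an active, mostly CBT-based TAU. It lies within the range of the CBT effects quoted (0.86 to 1.39), but the article ties it to none of them, and none is presented as an effect over usual care. Second, 1.0, .80 and 20% attrition lead to about 20 to 22 per arm, not 60, while 60 per arm gives over 99% power at 1.0. The 80% therefore describes neither the stated effect nor the contrast tested.

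The planned size has 80% power for d of about 0.58 with 48 per arm, or 0.52 with all 60. For assumed differences of 0.3 to 0.6, power at 48 per arm runs from about 31% to 83%. These figures assume a two-sided t-test at .05 on independent children. It does not follow that the trial is underpowered; that depends on a TDD-versus-TAU difference which the article does not give.

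**What to change.** In Sample size calculation:
- Remove 1.0 as the TDD-versus-TAU effect.
- State that the planned size has 80% power for a between-arm difference of about d = 0.58 (48 per arm after 20% attrition; 0.52 with 60 per arm), two-sided alpha .05, before any imputation loss, therapist clustering or gain from baseline adjustment.
- Show power at 48 per arm over an assumed range: about 31% at d = 0.3, 49% at 0.4, 68% at 0.5 and 83% at 0.6. Say that no prior TDD-versus-TAU estimate is available, or cite one if it exists.
- Keep any comparison with the earlier trial's 1.39 separate from the TDD-versus-TAU contrast.

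The cost is wording only, and N stays at 120. The downside is a less favourable power statement.
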